### Inclusion and Exclusion Criteria

Participants who meet the following inclusion criteria will be eligible for the study:

Diagnosed with primary open-angle glaucoma (POAG) [13]: open anterior chamber angle, pathologically high intraocular pressure (HIOP), with a peak IOP exceeding 21 mmHg (1 mmHg=0.133 kPa) within a 24-hour period, indicative of glaucomatous neuropathy (retinal nerve fiber layer defect [RNFLD] or optic disc changes) or visual field loss or both. Other causes resulting in HIOP were excluded for this diagnosis. Note that only 1 eye from each patient will be selected for examination.Having a visual field defect that can be assessed through standard automated perimetry with a reliability factor of less than 15%, as well as an IOP below 18 mmHg, at least 3 months after undergoing antiglaucoma surgery.Exhibiting a Chinese syndrome pattern associated with kidney deficiency and blood stasis.Refraining from the use of any other optic nerve protective agents, except for methylcobalamin, for a minimum of 2 months.Having a spherical refractive error ranging between +3.00 and –6.00 diopters, a fundus clearly visible without the need for pupil dilation, and a BCVA equal to or greater than 0.3.Within the age bracket of 18-75 years.In a conscious state and capable of cooperating with the examination and treatment process.Displaying a willingness to actively participate in the study and provide informed consent.

Participants who have any of the following conditions will not be eligible to participate:

Poorly controlled IOP (≤7 mmHg or >18 mmHg), accompanied by a thin filtering cystic bleb or bleb leakage.Glaucoma that is not open-angle glaucoma.A Chinese syndrome pattern that does not meet the criteria of kidney deficiency and blood stasis.Other conditions, such as macular degeneration, cataract, proliferative diabetic retinopathy, retinal vascular occlusion, or any other diseases that may cause visual field loss.Pregnancy or lactation.Abnormal primary liver or kidney function or serious systemic conditions, such as heart disease, primary hypertension, diabetes mellitus, or peptic ulcer disease.A history of allergic reactions to the ingredients of press-needle therapy or mecobalamin tablets.

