### Randomization and Allocation

Baseline evaluation will be conducted for eligible subjects. All eligible patients will be stratified according to early, moderate, and advanced stages of glaucoma [14]. Patients with early glaucoma exhibit early glaucomatous visual field impairment, as characterized by a mean deviation (MD) of >–6 dB. Conversely, patients with moderate glaucoma present a moderate glaucomatous visual field loss, defined as MD≤–6 to ≥–12 dB. Patients with advanced glaucoma experience advanced glaucomatous visual field loss, defined as MD<–12 dB. SAS software will be used to automatically generate a set of random numbers ranging from 001 to 192. These numbers will be further classified into 3 ranges based on the disease stage. The early stage will incorporate random numbers from 001 to 064, the moderate stage will encompass numbers from 065 to 128, and the advanced stage will comprise numbers from 129 to 192. Following stratification, the participants will be assigned randomly to either an experimental group or a control group in a 1:1 ratio. Random numbers will be inserted into identical envelopes of equal dimensions, which will then be sealed to ensure concealment of group allocation and minimize the risk of selection bias. The random sequence allocation will be preserved and withheld from the investigators, statisticians, and outcome assessors to avoid detection bias.

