### Outcome Measures

#### Primary Outcome Measures

The primary outcomes will enable us to evaluate improvements in visual function, retinal blood circulation, and retrobulbar blood vessel circulation due to press-needle therapy. The outcomes will be as follows:

The mean change in the BCVA will be measured at baseline and 4 weeks thereafter.The mean change in the values of the pattern standard deviation (PSD), mean defect, and square root of loss variance (sLV) will be determined using an Octopus 900 perimeter at baseline and 4 weeks thereafter.The whole-image vessel density (wiVD), radial peripapillary capillary vessel density (RPCVD), superficial macula vascular density (smVD), parafoveal vessel density (paraVD), perifoveal vessel density (periVD), macular ganglion cell complex (mGCC), and peripapillary retinal nerve fiber layer (pRNFL) will be determined using optical coherence tomography angiography (OCTA) at baseline and 4 weeks thereafter.The ophthalmic artery (OA), central retinal artery (CRA), short posterior ciliary artery (SPCA), peak systolic velocity (PSV), end diastolic velocity (EDV), and resistance index (RI) will be determined using CDFI at baseline and 4 weeks thereafter.

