### Statistical Analysis

Statistical analysis will be conducted independently by statisticians. The data will be presented as means (SDs). IBM SPSS 22.0 statistical software will be used. All statistical tests will be 2-sided tests, and the limit for statistical significance will be set at *P*<.05. The chi-square test will be performed for categorical variables, the independent Student *t* test will be used for measurement data, and the rank-sum test will be used for grade data. To evaluate the covariate balance, baseline characteristics will be summarized and compared between the experimental group and the control group using simple descriptive statistics.

Due to the expected low number of missing data, we will deal with missing data by transferring the last data item to the final dataset. This participant's data will be invalidated in the full analysis set (FAS), and this case will not be included in the per protocol set (PPS). Finally, the statistical significance of the FAS and PPS will be analyzed. A consistent statistical significance will indicate a significant difference.

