## Discussion

### Overview

Acupuncture is a major treatment in TCM, and studies have shown that acupuncture can protect the optic nerve in patients with glaucoma [20]. The press needle is a new kind of acupuncture device that can create a more lasting stimulus and simpler operation, while resulting in less pain, with the therapeutic effect of cumulative treatment characteristics. At present, press-needle therapy is widely used in various clinical diseases and has achieved satisfactory therapeutic effects [9,21]. Acupuncture is effective in protecting visual function in glaucoma [22]. Press-needle embedding can improve the deteriorating vision and shrinking visual field of patients with optic nerve atrophy and increase clinical efficacy [23]. Abnormal blood flow is an important factor in optic nerve damage in glaucoma [24], and acupuncture can modify the blood flow parameters in glaucoma [7]. Clinically, we have widely used press-needle therapy for glaucoma visual function protection and achieved good clinical efficacy, and we have further found that press-needle therapy can improve ocular circulation in patients with glaucoma. However, the quality of evidence supporting the use of press-needle therapy for GPCI is limited due to methodological limitations. Therefore, it is necessary to explore the effect of press-needle therapy on visual function and eye blood circulation in patients with GPCI. The double-blind method reduces the differential assessment of outcome events and improves subject adherence. Previous studies have shown that press needles and sham press needles (lacking the needle element) enable effective double-blind settings for acupuncture clinical studies [25]. Therefore, sham press needles were chosen as the control intervention for this study.

Due to the unique nature of glaucoma, patients experience progressive optic nerve damage as the disease progresses. To avoid violating medical ethics and reduce the rate of patient detachment, methylcobalamin has been chosen as the basic optic neuroprotective drug for the experimental and control groups in this study. In addition, to observe the effect of press-needle therapy on GPCI of different disease severities, participants will be classified as early, moderate, and advanced based on their visual field defects.

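### A pooled mean change in PSD or sLV has no single direction of benefit across early to advanced glaucoma, so neither index should be a primary outcome for visual function

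*Protocol article*

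**What the plan says.** The Primary Outcome Measures section of the protocol article gives the visual-field outcome as "The mean change in the values of the pattern standard deviation (PSD), mean defect, and square root of loss variance (sLV", taken at baseline and at week 4. It states the purpose of the primary outcomes: "The primary outcomes will enable us to evaluate improvements in visual function, retinal blood circulation, and retrobulbar blood vessel circulation".

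The Randomization and Allocation section stratifies by stage. Early disease is a mean deviation above –6 dB and moderate disease runs from –6 to –12 dB. For the last stage: "Patients with advanced glaucoma experience advanced glaucomatous visual field loss, defined as MD<–12 dB". No lower limit is given. The list gives each stage 64 of the 192 numbers, so that "the advanced stage will comprise numbers from 129 to 192".

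For continuous outcomes the Statistical Analysis section says that "the independent Student *t* test will be used for measurement data". The Overview in the Discussion says that severity classes are used "to observe the effect of press-needle therapy on GPCI of different disease severities", but attaches no analysis to that aim.

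**The concern.** By their names, one index is a standard deviation and the other the square root of a variance, so both describe the spread of local loss across the field. Mean defect, in the same sentence of the plan, describes the amount of loss. Local loss is bounded: a point can lose nothing, or everything the test can measure. Spread is therefore near zero when all points are normal and near zero again when all are lost, with a peak between. A fall in PSD or sLV can mean recovery on one side of the peak and deterioration on the other.

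The plan makes these two indices primary for improvement in a sample that may lie on both sides of the peak. A real gain could be diluted or hidden in them. A fall caused by worsening advanced eyes could be reported as benefit. With no fixed direction, a significant change either way could also be explained afterwards as favourable.

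**Working it through.** The plan has no figure of its own to reproduce here: its sample size rests on response rates and gives no expected change in PSD or sLV.

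**Inputs from the article.** Stage cut-offs at –6 and –12 dB. Advanced places 129 to 192, that is 64/192 = 33.3% of the list.

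**Assumptions, not in the documents.** A field in which a fraction f of points has lost D dB and the rest is normal; D = 20, 25 or 30; stage means of 4, 9 and 18 dB loss, written as positive m; equal stage sizes; the same 1 dB gain in mean defect in each stage.

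**Step 1: shape of the index.** With m = fD, the spread is D√(f(1–f)) = √(m(D–m)), which peaks at m = D/2: 10, 12.5 and 15 dB for D = 20, 25 and 30. For D = 30 it is 9.0 at 3 dB, 13.7 at 9 dB, 15.0 at 15 dB, 13.7 at 21 dB and 9.0 at 27 dB.

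**Step 2: recovery A, whole points return from lost to normal (D fixed, f falls).** Change = √((m–1)(D–m+1)) – √(m(D–m)). For D = 25 at m = 18: √(17×8) – √(18×7) = 11.66 – 11.22 = +0.44.

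| D | 4 dB | 9 dB | 18 dB | Mean of three | Mean of first two |
|---|---|---|---|---|---|
| 20 | –0.86 | –0.15 | +1.14 | +0.04 | –0.51 |
| 25 | –1.04 | –0.34 | +0.44 | –0.31 | –0.69 |
| 30 | –1.20 | –0.48 | +0.17 | –0.50 | –0.84 |

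Against early and moderate alone, pooling loses 54% at D = 25 and 40% at D = 30. At D = 20 the pooled effect is about zero. Conversely, at D = 25 a worsening from 18 to 19 dB lowers the index from 11.22 to √(19×6) = 10.68.

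**Step 3: recovery B, damaged points become shallower (f fixed, depth falls).** A 1 dB mean gain needs depth to fall by 1/f, so change = –√(f(1–f))/f = –√((D–m)/m). For D = 25 at m = 4: –√(21/4) = –2.29.

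| D | 4 dB | 9 dB | 18 dB | Mean of three | Mean of first two |
|---|---|---|---|---|---|
| 20 | –2.00 | –1.11 | –0.33 | –1.15 | –1.55 |
| 25 | –2.29 | –1.33 | –0.62 | –1.42 | –1.81 |
| 30 | –2.55 | –1.53 | –0.82 | –1.63 | –2.04 |

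The sign is the same in every stage. The pooled effect is 20% to 26% smaller than in early and moderate alone, but nothing cancels.

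**Step 4: recovery C, every point gains 1 dB.** Adding a constant does not alter a standard deviation, so the change is 0 in every stage.

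**Step 5: sensitivity to the advanced mean under A.** With D = 30, a 1 dB gain from 13 dB gives –0.17 and from 15 dB gives –0.03, so there is no reversal. With D = 25, a gain from 13 dB gives 0.00. A beta-distributed version of the field (concentration 1, D from 26 to 34, advanced means 15 to 24 dB) gives a ratio of pooled to early-and-moderate effect between 0.71 and 0.03. It has the same curve as A up to a constant factor, so it does not test mechanisms B or C.

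Mean defect improves by exactly 1 dB in every case above.

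**The case against.** The strongest reply is that opposite signs depend on the assumed recovery. If damaged points become shallower, benefit lowers the index at every stage. Nothing in the documents says that whole points would go from lost to normal within four weeks. This stands, and it rules out treating the 40% to 54% loss as an estimate for this trial.

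Near-complete cancellation also needs D = 20 with a mean loss of 18 dB, so 18/20 = 90% of points fully lost. That sits awkwardly with the eligibility requirements for an assessable field and "a BCVA equal to or greater than 0.3", although neither caps field loss. This too stands: cancellation is an extreme case.

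Mean defect is primary as well and would show a mean field gain or expose worsening. That is correct, and it limits the harm. It does not give PSD or sLV a direction of their own, and each is listed as primary in its own right.

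Finally, an analysis plan that is not shown may analyse by severity, and the Overview hints at it. That is possible. But the article already fixes the mean change in both indices as primary, and a stratified analysis would not by itself turn a measure of unevenness into a measure of improvement.

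**Conclusion.** The concern holds in a limited form. As primary measures of improved visual function, PSD and sLV have no single direction of benefit in a sample running from early to advanced disease. For the same gain in mean defect, their pooled change may keep its sign, be diluted, be zero or, in one extreme assumed case, cancel. Which of these applies depends on how points recover and how advanced the eyes are. The documents give neither, so the size cannot be fixed.

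A reader might infer more, and three such readings are not supported:

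- That a real benefit will cancel, or that these indices can never be interpreted. Recovery B gives a consistent sign throughout.
- That one third of the sample has a reversed direction. The 64 of 192 are places on the randomisation list, not observed enrolment, and not every eye below –12 dB is past the peak.
- That the visual-field conclusion as a whole is unsafe. Mean defect moves in one direction and is unaffected.

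**What to change.** Before unblinding, name mean defect as the only visual-field primary variable and make PSD and sLV supportive. Report both for all randomised patients and by the three existing severity strata. Interpret them only together with mean defect, and claim no benefit from a change in PSD or sLV alone.

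Restricting the two indices to early and moderate disease is not a sound alternative. It would drop up to a third of the randomised places. With D = 20 the peak of 10 dB also lies inside the moderate stratum: under recovery A, a 1 dB gain from 12 dB changes the index by √(11×9) – √(12×8) = +0.15, so signs would still mix.

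The cost is amendment wording and its submission to the ethics committee, which the Ethical Considerations section already requires for a change of outcomes. No new data are needed. The Results section places data processing and analysis in October 2025, so the change should precede that step. The downside is that PSD and sLV no longer count as primary.

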#### Secondary Outcome Measures

The following secondary outcomes will help us determine whether press-needle therapy improves TCM clinical symptoms and changes in the IOP:

The mean change in the IOP in the study eye will be determined uisng a TX-20P full autotonometer at baseline and at 1, 2, 3, and 4 weeks thereafter.Changes in TCM symptoms will be assessed by the investigators trained in SOPs according to the TCM Symptom Score Scale (Table S1 in Multimedia Appendix 1) at baseline and at 1, 2, 3, and 4 weeks thereafter.

### Safety Evaluation and Adverse Events

Safety assessments using 3 routine tests (blood, urine, and stool), electrocardiography, liver function tests (alanine aminotransferase [ALT], aspartate aminotransferase [AST], alkaline phosphatase [ALP], gamma-glutamyl transferase [GGT], and serum total bilirubin [TBIL]) and kidney function tests (blood urea nitrogen [BUN], serum creatinine [SCr], uric acid [UA], and β 2-microglobulin) will be measured at baseline and 4 weeks thereafter.

A research assistant will monitor and record data regarding adverse events (AEs) associated with interventions, which may include infection, hematoma, severe pain, needle breakage, bleeding, heart palpitations, fainting, and headaches, in case report forms (CRFs). Severe AEs will be managed by emergency medicine physicians or acupuncturists. Additionally, any significant AEs will be reported to the Ethics Committee of the Mianyang Central Hospital.

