#### Criteria for Discontinuing or Modifying Allocated Interventions

Participants will have the freedom to withdraw from the clinical study and opt for alternative treatments (eg, citicoline sodium tablets) if they believe their condition will not improve. Reasons for discontinuing treatment may include, but are not limited to, the following: (1) the pregnancy, (2) severe side effects or complications, (3) taking other medications during the study, (4) failure to comply with the study protocol, and (5) request for withdrawal for other reasons.

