### Data Collection and Quality Control

Thorough recording of all data will be performed on CRFs subsequent to in-person visits or telephonic communications with participants. The same examiner will assume responsibility for conducting the examination of every patient during each assessment. Baseline measurements, demographics, medical history, and prior medications will only be gathered during the initial visit. Primary outcomes, secondary outcomes, and safety indicators will be gathered at baseline and 4 weeks thereafter. Following adequate training and successful completion of a test, 2 data entry clerks will thoroughly review the CRFs and subsequently enter the collected data independently. Participants’ personal information will be kept confidential the same way as their medical histories in the hospitals before, during, and after the trial. The absence of a data monitoring committee in this study is justified by the anticipated low incidence of AEs and the limited participant numbers at each center. The Epidata 3.1 statistical application will be used for data entry. Subsequently, the collected data will be transferred to IBM SPSS 22.0 statistical software for the purpose of analysis.

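### As written, the missing-data rule gives a participant without week-4 laboratory and ECG tests either the baseline result or no result, and harm-related leaving then biases that comparison towards no difference

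*Protocol article*

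**What the plan says.** Safety is part of the trial's objective (Abstract, Objective). Under Safety Evaluation and Adverse Events, the article lists "Safety assessments using 3 routine tests (blood, urine, and stool), electrocardiography, liver function tests" and kidney function tests, and says that these "will be measured at baseline and 4 weeks thereafter". Data Collection and Quality Control repeats the schedule: "Primary outcomes, secondary outcomes, and safety indicators will be gathered at baseline and 4 weeks thereafter". Neither section mentions a test between the two time points or on leaving early.

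The section on discontinuing or modifying interventions lists "severe side effects or complications" among the reasons for stopping, and says that participants are free to withdraw from the study.

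On missing values, Statistical Analysis says "we will deal with missing data by transferring the last data item to the final dataset". Its next sentence says that the participant's "data will be invalidated in the full analysis set (FAS), and this case will not be included in the per protocol set (PPS"). It then says "the statistical significance of the FAS and PPS will be analyzed". No type of data is excepted from these rules, and no set other than the FAS and PPS is named.

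Adverse events have a separate route. A research assistant monitors them and records them on case report forms, and significant ones are reported to the ethics committee.

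**The concern.** With only two scheduled time points, the last available item for a participant without week-4 tests is the baseline result. The two sentences on missing data then give different answers. The first enters the baseline result as the final one. The second voids the participant's data in the FAS and removes the case from the PPS. The article does not say which sentence governs.

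For safety data neither answer is neutral if people leave because of harm. Carry-forward replaces a possible abnormality with an unchanged value, and exclusion removes the person in whom it may have occurred. The eligibility criteria exclude abnormal primary liver or kidney function, so a carried-forward liver or kidney result would usually be normal.

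At stake is the between-arm comparison of laboratory and ECG results, which would look more reassuring than it should. The trial has no data monitoring committee (Data Collection and Quality Control), so the final safety tables carry more weight.

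**Working it through.** The article states no figure for this point, so there is none to reproduce. The check has two parts.

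**1. Following the text for one participant who leaves before the week-4 tests**

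- Available laboratory and ECG data: baseline only.
- Carry-forward sentence: final value = baseline value, so change = 0, whatever the baseline value was.
- Next sentence: data void in the FAS and case not in the PPS, so no contribution to either named set.

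**2. Size**

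The documents give no abnormality rates, so the rates here are assumptions. Let p be the true rate of an on-treatment laboratory or ECG abnormality in the experimental arm, and f the share of affected participants there who have no week-4 test. Assume normal baseline values, no loss among unaffected participants and no loss in the control arm. The observed experimental rate is then

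- carry-forward: p(1 − f)
- exclusion: p(1 − f) / (1 − pf)

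Worked case: p = 0.10, control rate 0.02, f = 0.5.

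- True difference: 10 − 2 = 8.0 points.
- Carry-forward: 0.10 × 0.5 = 0.050, and 5.0 − 2.0 = 3.0 points.
- Exclusion: 0.050 / (1 − 0.05) = 0.0526, and 5.26 − 2.0 = 3.3 points.

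Observed difference in percentage points over the range of f:

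| f | 10% v 2%, carry-forward | 10% v 2%, exclusion | 5% v 1%, carry-forward | 5% v 1%, exclusion |
|---|---|---|---|---|
| 0 | 8.0 | 8.0 | 4.0 | 4.0 |
| 0.25 | 5.5 | 5.7 | 2.75 | 2.8 |
| 0.50 | 3.0 | 3.3 | 1.5 | 1.6 |
| 0.75 | 0.5 | 0.7 | 0.25 | 0.3 |
| 1 | −2.0 | −2.0 | −1.0 | −1.0 |

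Both routes move the same way and differ little. The size turns almost wholly on f, which the documents do not give. At f = 0 there is no bias.

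The only guide to the amount of missing data is the dropout allowance under Sample Size Calculation: 160 × 20% = 32 added, and 32/192 = 16.7% of those recruited. This is dropout for any reason and does not estimate f.

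**The case against.** The strongest case against is that this is a condensed article. Safety sets and rules for counting adverse events are usual content of an analysis plan, which is not shown. Statistical Analysis never mentions safety, and its closing rule on agreement between FAS and PPS reads like an efficacy rule. This stands in part: the absence of a safety set alone would be no finding. But the article does state a missing-data rule, without restriction, and contradicts it in the next sentence. That is a defect in what is written.

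A reader might go further and infer that adverse events recorded before withdrawal would be counted in neither set. The documents do not support this. Adverse events go onto case report forms independently of the week-4 tests, and Statistical Analysis does not say that its rules govern adverse-event counts. The local events the article lists, such as infection, hematoma, bleeding and severe pain, belong to that route, so carrying laboratory values forward does not touch them.

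Nor does stopping treatment necessarily mean missing the week-4 tests. The article does not say that testing ends with treatment, so the bias arises only for those who are not tested.

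Normal baseline results are an inference. The eligibility criteria support it for liver and kidney function, but set no explicit requirement for urine, stool or ECG results. The change of 0 under carry-forward does not depend on it.

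Finally, the article expects few missing data and a low incidence of adverse events. If both prove right, the effect is small.

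**Conclusion.** The point holds for the laboratory and ECG comparison. The missing-data sentences contradict each other and, applied to tests taken only at baseline and week 4, both bias that comparison towards no difference if leaving is related to harm. The size rests on the unknown share of affected participants without week-4 tests. In the illustration, a true difference of 8.0 points falls to about 3 if that share is one half, and is unchanged if it is zero. The abnormality rates are assumptions.

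Two stronger readings should be set aside.

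- *That the trial would miss severe side effects altogether.* One could assume a 5% rate among 96 participants (4.8, about 5), remove 20% (96 × 0.8 = 76.8, about 77), and report 0/77 with an exact two-sided 95% upper limit of 1 − 0.025^(1/77) = 4.7%, against 5/96 = 5.2%. The arithmetic is right, but it presumes that every affected participant is lost and that no recorded event is counted. The article says neither.
- *That 220 − 192 = 28 recruits (28/220 = 12.7%) show harm-related loss.* The article gives no reasons for these 28, and its Abstract says that the remaining participants will allow exploration of interactions. They cannot be read as withdrawals for harm.

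Confidence is medium, because the full protocol or analysis plan may already confine these rules to efficacy. The correction is still worth making: the rule is wrong for safety data as written, and changing it costs little.

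**What to change.** In Statistical Analysis:

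1. Reconcile the two missing-data sentences, and state that carry-forward and the FAS/PPS rules apply to efficacy outcomes only.
2. Analyse laboratory and ECG safety data from observed values, without carrying baseline forward, and report the number missing per arm.
3. Summarise adverse events for all participants who received at least one real or sham press-needle application, counting every event recorded up to last contact, whether or not the participant completed.

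The cost is a few sentences and one set of tables from data already on the case report forms, with no new visits, tests or participants. The downside is fewer laboratory and ECG values at week 4 and possibly slightly less favourable safety figures. Observed-value analysis does not recover results that were never obtained, which is why the number missing per arm needs to appear beside it.

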**Objective:**

The objective of the trial is to evaluate the safety and clinical efficacy of press-needle therapy and investigate whether it can improve visual function by regulating eye blood circulation in patients with GPCI.

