#### Blinding

The researcher assistants, outcome assessors, statisticians, and subjects will be blinded to the group assignment. All participants will undergo press-needle therapy while lying on a bed in a tranquil clinic setting. For the control group, a nonpenetrating sham apparatus, similar in appearance to acupuncture needles, will be used to achieve blinding. Moreover, every participant will be asked about their experience subsequent to the acupuncture session to evaluate the efficacy of blinding. Unblinding of researchers is permitted only in exceptional circumstances, such as when there is a strong need to know about the actual treatment in order to manage the subject appropriately.

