#### Control Group

Sham press needles are the same as press needles but lack the needle element [9]. The procedures and manipulations carried out in the control group will be indistinguishable from those implemented in the experimental group. Subjects will be treated individually in a secluded room to prevent any disruptions from family members or other individuals.

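### Adverse event recording is limited to events associated with the interventions, so absolute rates will be understated and the between-arm comparison may be biased if attribution differs by arm

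*Protocol article*

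**What the plan says.** The abstract of the protocol article names safety first: "The objective of the trial is to evaluate the safety and clinical efficacy of press-needle therapy". In the Methods, Safety Evaluation and Adverse Events sets up three separate streams:

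- **Scheduled tests at baseline and week 4.** "Safety assessments using 3 routine tests (blood, urine, and stool), electrocardiography, liver function tests" and kidney function tests are done, with no condition on cause.
- **AEs on the case report form (CRF).** A research assistant is to "monitor and record data regarding adverse events (AEs) associated with interventions". An open list of eight examples follows. Some concern the needle or the skin, such as hematoma and needle breakage. Others are general, such as palpitations, fainting and headaches.
- **Escalation.** "any significant AEs will be reported to the Ethics Committee of the Mianyang Central Hospital", again with no condition on cause.

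Two other sections bear on the point. Under Blinding, "The researcher assistants, outcome assessors, statisticians, and subjects will be blinded to the group assignment". Under Control Group, "Sham press needles are the same as press needles but lack the needle element". No section says that AEs are recorded regardless of cause.

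**The concern.** A randomised sham-controlled trial gives its most direct evidence on clinical harm by counting every event in both arms and comparing the counts. Here entry on the CRF depends on an event being associated with the interventions. That is a stated scope, so it cannot be put down to detail that a journal article leaves out.

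Three things are at stake. First, events not linked to the intervention drop out, so the reported rate is too low in each arm. Second, unexpected symptoms are the events least likely to be recognised as associated, and scheduled tests four weeks apart may not show them. Third, association may be seen differently in the two arms. Some listed examples, such as needle breakage, cannot arise from a device without a needle, and a participant or recorder who guesses the allocation may attribute the same symptom differently.

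The plural term also leaves open whether events from methylcobalamin, which the Discussion gives as basic treatment in both arms, are within scope. In addition, Data Collection and Quality Control justifies having no data monitoring committee partly by an expected low incidence of AEs. A recording rule that lowers the count would seem to bear that expectation out.

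**Working it through.** The plan states no figure on this point, so there is none to reproduce. The check has two parts.

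**1. Which safety data pass through the filter**

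| Data | Section | Limited by cause? |
|---|---|---|
| Blood, urine and stool tests, ECG, liver and kidney function | Safety Evaluation and Adverse Events | No |
| Visual acuity, visual field, OCTA, Doppler imaging | Primary Outcome Measures | No |
| Intraocular pressure at baseline and weeks 1 to 4 | Secondary Outcome Measures | No |
| Significant AEs sent to the ethics committee | Safety Evaluation and Adverse Events | No |
| AEs recorded on the CRF | Safety Evaluation and Adverse Events | Yes |

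Only the CRF record of AEs is affected. It is also the only systematic source described for symptoms that come and go between visits. The ethics report is an escalation route for significant events and does not replace that record.

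**2. What the filter does to rates and ratios**

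Let p be the true risk that a participant has an AE, and r the probability that such a participant is recorded because the event counts as associated. Subscript T is press needle and C is sham.

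- Recorded risk in an arm = p × r
- Recorded risk ratio (RR) = (p_T / p_C) × (r_T / r_C)
- Recorded risk difference = p_T r_T − p_C r_C

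From the document: 1:1 allocation and 192 participants, so 192 / 2 = 96 per arm. Assumed, because the document gives neither: every p and every r.

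| True risk T, C | r_T, r_C | Expected recorded per 96 (T, C) | Recorded RR | True RR |
|---|---|---|---|---|
| 10%, 10% | 1, 1 | 9.6, 9.6 | 1.00 | 1.00 |
| 10%, 10% | 0.5, 0.5 | 4.8, 4.8 | 1.00 | 1.00 |
| 10%, 10% | 0.7, 0.5 | 6.7, 4.8 | 1.40 | 1.00 |
| 10%, 10% | 0.8, 0.3 | 7.7, 2.9 | 2.67 | 1.00 |
| 10%, 10% | 0.8, 0.2 | 7.7, 1.9 | 4.00 | 1.00 |
| 15%, 10% | 0.5, 0.5 | 7.2, 4.8 | 1.50 | 1.50 |
| 15%, 10% | 0.7, 0.5 | 10.1, 4.8 | 2.10 | 1.50 |

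Worked example, third row: 0.10 × 0.7 × 96 = 6.72 and 0.10 × 0.5 × 96 = 4.80; RR = 0.07 / 0.05 = 1.40.

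Three results follow:

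- Whenever r is below 1, the recorded rate is too low in that arm.
- With equal r the ratio is preserved but the difference shrinks. For true risks of 15% and 10% with r = 0.5, the difference falls from 5.0 to 7.5 − 5.0 = 2.5 percentage points.
- The ratio is biased only if r_T differs from r_C, and the direction is not fixed. Reversing the third row gives 0.05 / 0.07 = 0.71.

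**The case against.** The strongest reply has four parts.

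- **The phrase may be loose.** It could mean AEs arising during treatment. The article describes no causality judgement, nobody who makes one and no gate before CRF entry. A reader might infer that the research assistant must rule on cause first and that unrelated events are never captured; the text does not go that far. The example list is open and includes events that could occur under sham. This limits how firmly the procedure can be described. It does not supply all-cause recording, which appears nowhere, and the plain sense of the sentence is a restriction.
- **Blinding protects the comparison.** The recorder and the participants are to be blinded, so the filter is not differential by design. This stands: with equal attribution the risk ratio is intact. Blinding does nothing for the absolute rates, and it may weaken when one device has no needle. The plan itself intends to ask participants about their experience in order to evaluate blinding.
- **Other safety data are unfiltered.** This also stands. A reader might infer that ocular harm would be hidden, but acuity, field, imaging and pressure are measured in both arms whatever the presumed cause. Only ocular symptoms that those measures do not show could be missed.
- **The article is condensed, and safety is not among its Methods objectives.** AE definitions and CRF layout may well sit in the full protocol, and their absence is no finding. The point here is the scope that the article does state. Research Objectives names only efficacy and mechanism, but the abstract makes safety an objective and the Methods give it a section of its own.

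**Conclusion.** The point holds in a limited form, as a correction that should be made. The stated scope for CRF recording is narrower than a safety objective needs. Followed as written, it understates absolute AE rates and can miss unexpected symptomatic events between the two rounds of tests. Bias in the between-arm AE comparison is a risk that depends on attribution differing by arm.

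A reader might conclude that the safety objective cannot rest on any unbiased comparison, or that randomisation is lost for safety. The documents do not support that: the laboratory, ECG, visual function and intraocular pressure comparisons do not pass through the filter, and the blinding described would keep the AE ratio unbiased if it holds.

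The size cannot be taken from the document, which calls AE incidence low and gives no figure. The recorded ratios of 1.00 to 4.00 under equal true risks show how the mechanism works on assumed inputs and are not estimates for this trial. Nor can an assumed share of unrelated events be turned into a number of participants lost, because someone with one recorded and one unrecorded event still appears in the data.

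**What to change.** Change the sentence in Safety Evaluation and Adverse Events so that:

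- all AEs in both arms, from first application to week 4, are recorded on the CRF regardless of relation to the interventions;
- relatedness and severity are separate CRF fields, completed blinded to allocation;
- the existing examples stay as events to ask about, in the same way in both arms;
- all-cause AEs are compared by arm, with related AEs shown separately.

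For participants already treated, the report should say that the narrower rule applied. How many could still benefit is unclear, because Results gives recruitment both as February 2023 to March 2024 and as continuing until September 2025. If all AEs were in fact being recorded, one clarifying sentence to that effect settles the matter.

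The cost is a few more CRF entries by the same research assistant, with no added visits or staff.
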